### Knowledge, attitudes, perceptions of depression and available services

Participants’ knowledge, attitudes, and perceptions regarding depression and available services will be assessed during a three-month follow-up. Three structured questionnaires, each with four response options, have been developed based on the intervention content. The knowledge about depression scale consists of 7 items, the stigma and myths scale consists of 5 items, and the knowledge about available services scale consists of 8 items. These scales will be asked during the three-month follow-up, not at baseline. Each question will have one correct response and three incorrect responses. Participants will choose the correct response for each question after a research assistant reads the question and all possible responses. Composite scores will be calculated based on the number of correct responses for each scale for analysis. We will report the number of correct responses in each domain: knowledge, attitudes, and perceptions on depression. Additionally, we will also use continuous scores (i.e. total score of each domain) when performing mediator analysis.

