### Mediators

Previous studies have demonstrated a positive correlation between mental health literacy, attitudes, stigma, and symptom severity in relation to help-seeking behaviour [10, 11, 29, 69]. Our formative study also indicated that individuals who were familiar with depression symptoms and aware of mental health service providers and locations were more inclined to seek help from health care providers. Therefore, we aim to investigate whether participants’ knowledge, attitudes, and stigma can act as mediators in influencing help-seeking behaviour. Furthermore, we will also assess the symptom severity of depression, as measured by the PHQ-9 at a three-month follow-up, to determine if it plays a mediating role in help-seeking behaviour. We will use the Baron and Kenny method along with a path analysis to examine the mediation effects. For the Baron and Kenny method, a series of general linear regression models will be tested to assess mediation [49]. Mplus will be used to conduct a path analysis looking at the direct and indirect effects to determine if the hypothesized mediator is in fact a mediator in the relationship between the predictor variable and outcome of interest [19].

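### The scales reported and tested as attitude, perception and stigma mediators are number-correct scores with keyed answers, so an indirect effect through them supports mediation by knowledge or beliefs, not by attitude or stigma change

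*Protocol article*

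**What the plan says.** The section on knowledge, attitudes and perceptions of depression and available services describes the instruments. "Three structured questionnaires, each with four response options, have been developed based on the intervention content". It names three scales: "The knowledge about depression scale consists of 7 items", "the stigma and myths scale consists of 5 items", and a scale on knowledge of available services has 8. On format, "Each question will have one correct response and three incorrect responses". On the respondent's task, "Participants will choose the correct response for each question after a research assistant reads the question and all possible responses". On scoring, "Composite scores will be calculated based on the number of correct responses for each scale for analysis".

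The same section then labels the results: "We will report the number of correct responses in each domain: knowledge, attitudes, and perceptions on depression". It adds that the total score of each domain enters the mediator analysis.

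The mediators are listed twice. Under Outcome measures, Mediators, they are knowledge, attitude and perception of depression, plus symptom severity. Under Quantitative data analysis, Mediators, the aim reads "we aim to investigate whether participants’ knowledge, attitudes, and stigma can act as mediators in influencing help-seeking behaviour", with PHQ-9 severity added. Perception appears only in the first list and stigma only in the second.

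**The concern.** The names of the mediators and the content of the scales do not match. An attitude or a perception has no correct answer, yet every item described has one. A participant may choose the keyed fact over a myth and still hold a negative attitude towards people with depression, or towards seeking care.

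The protocol's own rationale points to a different construct. The references given for the mediators are cited in the Introduction for internalised stigma and for attitudes and intentions towards seeking help. The Introduction also assigns the change of negative attitudes to the recovery story. The three scales correspond to the other three components, so the component meant to shift attitudes has no scale of its own.

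If the plan is followed as written, a report could state that attitudes or stigma mediate help-seeking when the score behind the statement counts correct answers on content related to the intervention. The mechanism claim would then be broader than the measurement.

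**Working it through.** The plan gives no figure to reproduce here. The check sets the scales against the labels.

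**Inputs** (all from the section describing the scales, unless stated)
- Scales: knowledge about depression, 7 items; stigma and myths, 5; knowledge about available services, 8.
- Format: four options, one keyed correct; score = number correct.
- Reported domains: knowledge, attitudes, perceptions.
- Mediators tested: knowledge, attitude, perception (Outcome measures); knowledge, attitudes, stigma (Quantitative data analysis).
- Components by condition: Randomization, Table 1.

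**Step 1: items by scale name.** Total items = 7 + 5 + 8 = 20. Items on scales named knowledge = 7 + 8 = 15 of 20. Items on the only stigma-related scale = 5 of 20. Scales named attitudes or perceptions = 0.

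**Step 2: can three scales fill three domains?** No mapping is given, so try both kinds.
- One scale per domain: two scales are named knowledge but only one domain is. At least one knowledge scale must then be reported as attitudes or perceptions.
- Both knowledge scales in the knowledge domain: the 5-item stigma and myths score is all that is left. It must serve for attitudes and perceptions, and also for stigma in the analysis section.

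Neither mapping gives a separate measure of attitudes and of perceptions.

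**Step 3: what the stigma and myths score can show.** The intervention section on stigma, myths and facts says that this component covers stigma and stigmatised behaviours, then sets myths against facts. The scale was developed from the intervention content and counts correct answers. A rise in the score when the component is on shows that participants more often choose the keyed answer. If the score is also related to help-seeking, the indirect effect runs through knowledge or beliefs about stigma and myths. Nothing described lets that be extended to attitudes towards seeking care or to internalised stigma.

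**Step 4: which scores correspond to a randomised factor.** From Table 1, with 36 per condition:
- Stigma component on in conditions 1, 2, 5 and 6: 4 × 36 = 144. Off in 3, 4, 7 and 8: 144.
- Services component on in conditions 1 to 4: 144. Off in 5 to 8: 144.
- Information about depression on in all eight: 8 × 36 = 288. Off: 0.

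The stigma/myths and services scores can therefore be compared by component on or off (planned numbers, before any loss to follow-up). The depression score has no matching contrast.

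**The case against.** The strongest reply is that the items are not shown. This is a journal article, and item wording, piloting and any validation may sit in the full protocol. Questions on the same topics as the intervention need not repeat the taught sentences. Accepting or rejecting myths is also part of the belief side of stigma, so a keyed item can be a narrow proxy for it. In mediation, a component is expected to move its proximal target; that is the first path, and the link from the score to help-seeking is not built in. Finally, the mediators are neither the primary nor the secondary outcome, and the article does not make them a criterion for choosing components.

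Most of this stands, and it limits the point. A reader might infer that the scales are pure recall tests that rise by construction, or that the trial can say nothing about stigma. The documents do not support either reading: the items are unseen, the scales are given at three months, and the myths content touches beliefs that belong to stigma. Nor do guessing scores help. With four options the expected score by chance on the 5-item scale is 5/4 = 1.25, but that bears on reliability, not on which construct is measured.

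The reply does not rescue the labels. Keyed answers, number-correct scoring and the scale names are stated outright, and item wording or validation data would not by themselves align the domain names with the scales described.

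**Conclusion.** The point holds as one of labelling and of the reach of the mediation claim. Two of the three reported domains, attitudes and perceptions, have no corresponding scale. The only stigma-related score is a 0 to 5 count of correct answers. Mediation through it may be reported as mediation by knowledge or beliefs about stigma and myths, not as attitude or stigma change.

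This rests on the format, scoring and scale names in the article, and on the assumption that no further attitude or stigma measure exists in a document not shown. It does not depend on the timing of the scales or the choice of mediation method. The consequence is confined to conclusions about mechanism: the main effects of the components on help-seeking, and treatment adherence, are untouched.

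**What to change.** 1. In both Mediators sections and in the section describing the scales, use one set of names taken from the scales: knowledge about depression; knowledge or beliefs about stigma and myths; knowledge about available services. Keep symptom severity as a separate entry. Drop attitudes and perceptions as domain and mediator names.
2. State that any indirect effect through these scores will be interpreted as mediation by knowledge or beliefs only.
3. Tabulate the stigma/myths score by stigma component on or off, and the services score by services component on or off. Present this as a supplementary delivery and contamination check beside the checklist in the section on fidelity, which already records content from components not allocated to a session. The Discussion expects participants to ask FCHVs for such content. Because the scales are not given at baseline, a high score with the component off may reflect prior knowledge as well as leakage, so it should prompt a look at the checklists and not be read alone. The depression score cannot be used this way, because every condition receives that component.

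The cost is a few changes of wording, two small tables from data already planned, and a narrower claim about mechanism. No new instrument or data are needed. Replacing the scale is not part of this fix: the questionnaires already exist and the Timeline puts the start of baseline data collection in July 2024, so a swap would risk mixing instruments within the trial.

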### Symptom severity

The severity of depression symptoms will be assessed using the locally validated Patient Health Questionnaire (PHQ-9) three months after treatment initiation. The PHQ-9 is a nine-item tool commonly used to evaluate depression symptoms. Participants will rate nine common symptoms of depression based on their experiences over the previous two weeks using a 4-point scale ranging from 0 (not at all) to 3 (always) [24]. The PHQ-9 has been translated, culturally adapted, and validated in Nepal with a sensitivity of 0.94 and specificity of 0.80 for the recommended cut-off score of ≥ 10 for screening individuals with depression [42]. We will use the total scores of the PHQ-9, which range from 0 to 27, to examine the mediating effects of depression symptom severity in individuals seeking help. A higher score on the PHQ-9 indicates a more severe level of depression [24].

### Implementation measures

Data on fidelity, feasibility, acceptability, and appropriateness of the intervention delivered by FCHVs in community settings will be collected for each intervention component and delivery strategy.

### Fidelity of the implementation of Gain Life

Fidelity in implementing the components and combination of components in the Gain Life intervention will be assessed by two supervisors. They will observe sessions and engage with Female Community Health Volunteers (FCHVs) within 24 h of the intervention. A structured fidelity checklist will be utilized to evaluate the skills, content, and delivery methods of each intervention component. The checklist is based on the content and delivery methods outlined in different components of the intervention. It will ascertain if FCHVs covered all the methods and content in a particular component, and if they incorporated content from other components not included in that session. Supervisors will observe at least two sessions of each FCHV, and two fidelity checklists will be completed through discussions with the FCHVs within 24 h of the intervention.

### Feasibility, acceptability and appropriateness

The feasibility, acceptability, and appropriateness of the intervention will be evaluated using qualitative methods, including individual interviews (IDIs) and focus group discussions (FGDs). FGDs will involve Female Community Health Volunteers (FCHVs) who implemented the intervention to assess their experience with using the CIDT to identify individuals with depression and implementing the Gain Life intervention. Each focus group will include six to eight FCHVs.

Individual interviews will be conducted with three participant groups: those who did not receive treatment, those who started but discontinued treatment, and those who are still receiving care three months after participating in the Gain Life intervention. Some interviews will also involve family members who attended the intervention. Interviews with participants who did not start the intervention will take place two months after their participation, while interviews with the other two groups (those who dropped out and those still receiving care) will occur after a three-month follow-up period.

### Process evaluation

The implementation process, including training and supervision of FCHVs, as well as barriers and facilitators of the intervention, will be documented by a separate individual through observation of training and supervision sessions and interviews with supervisors.

### Data management and analysis

Quantitative data will be collected using an Android tablet with questionnaire applications. The data will be stored in the TPO Nepal server. Data collected on the ODK platform will be transferred to the TPO Nepal server, and any inconsistencies in data collection will be monitored regularly by the research supervisor. Inconsistencies and errors in the data will be minimized manually.

### Quantitative data analysis

Quantitative data analysis will be conducted using StataIC 15.1 and MPlus (v8) [60]. Baseline characteristics of the participants (such as age, sex, caste/ethnicity, education) will be compared to assess balanced randomization. An intent-to-treat model will be used. Participants who do not receive all allocated intervention components for various reasons will be included in the intent-to-treat analysis. Despite the short three-month interval between the baseline and follow-up interviews, there is a risk of participant dropout during the follow-up period, possibly due to work-related mobility. To address this issue, we also plan to conduct the follow-up interviews via phone to minimize the risk of dropout. Any missing data or loss to follow-up will be carefully examined, and if necessary, we will utilize multiple imputation techniques to handle missing data effectively.

### Primary outcome

As recommended for factorial designs, effect coding will be utilized for all analyses [13]. The primary outcome of interest is change in help-seeking behaviour. This will be evaluated by determining the proportion of participants who attended the Gain Life intervention and sought care from health care providers rather than traditional or religious leaders. This will be measured by the number of participants who received the Gain Life intervention and sought treatment from health care providers. General linear regression models will be used to test the main effects of the Gain Life intervention components and their association with the primary outcome of interest [52].

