### Study design

This is a single-blinded, individually randomized factorial trial. Behaviour change interventions are complex due to the many interacting components involved [15]. While traditional randomized controlled trial (RCT) designs are considered the gold standard for evaluating the impact of an intervention, they typically do not identify which specific components contribute to desired outcomes [13]. In contrast, factorial design enables the assessment of individual intervention components and their interactions [36]. This approach is appropriate for enhancing the effectiveness, efficiency, and cost-effectiveness of an intervention, ultimately facilitating its scalability to benefit a large population [14].

In this study, we will utilize a Multiphase Optimization Strategy (MOST), an engineering-based approach aimed at effectively optimizing behavioural interventions [13]. MOST comprises three key phases: preparation, optimization, and evaluation. The preparation phase involves developing a conceptual model for the intervention and piloting it to identify “core components” and determine the optimization criteria (e.g. effectiveness, efficiency, cost). The optimization phase utilizes a multifactorial design to conduct a randomized factorial experiment trial using the specific components identified during the preparation phase. Finally, the evaluation phase involves reviewing the trial results and reaching a consensus on the way forward. We will conduct a 2 × 3 factorial individually randomized, single-blinded controlled trial design. Participants detected by Female Community Health Volunteers using the CIDT, will be randomized into one of eight possible combinations of three candidate intervention components ranging from none to all three components (*n* = 36 in each condition). All participants will receive component one, i.e. information about depression. However, the three candidate intervention components, each with two options, include the following: (a) information about available services (on/off), (b) addressing stigma and discrimination (on/off), and (c) life transformation recovery stories (on/off). All four intervention components will be delivered in person on a one-to-one basis.

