### Sample sizes and sampling process

The sample size for this study was determined based on the need to detect a difference in help-seeking behaviour between participants receiving the mental health literacy component (i.e. information about depression) alone (40%) and those receiving both the mental health literacy and stigma, myths, and facts about depression components (60%) [32, 53]. With 90% power and a significance level of 0.05, a total sample size of 288 participants is required, with 36 participants per condition. This sample size will allow to determine which component of the Gain-Life intervention positively impacts the primary outcome of help-seeking behaviour among individuals with depression.

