### Randomization

Participants will be randomly assigned to one of eight treatment conditions based on four factors: (i) information on depression, (ii) available treatments, (iii) stigma reduction through myths and facts, and (iv) life transformation experiences. Using Microsoft® Excel (Version 16.86), a list of random numbers between one and eight with no duplicates was generated for each FCHV. As the FCHVs enrol participants, the first author assigns the next random number on their list to each participant, indicating the allocated treatment condition. Because each FCHV will recruit between 8 and 10 participants and there are only 8 treatment conditions, some FCHVs ended up delivering each condition at least once, and some conditions will be delivered twice. The table below summarizes the allocation of participants into different intervention components.

The first author will randomize each case using a computer-generated random table and assign them to one of the eight factors presented in Table 1 below. The randomization will be conducted separately for each FCHV to ensure cases are allocated to all 8 factors. The first author will inform the supervisors of the randomization results within 24 h. The supervisors will then inform FCHV which intervention or combination of interventions should be delivered to each case via a phone call.

**Table 1 Tab1:** Random allocation of participants into different intervention components

Experimental condition/factors	Information about depression	Information about available services	Stigma reduction	Recovery story (video)	Sample size
1	**✓**	**✓**	**✓**	**✓**	36
2	**✓**	**✓**	**✓**		36
3	**✓**	**✓**		**✓**	36
4	**✓**	**✓**			36
5	**✓**		**✓**	**✓**	36
6	**✓**		**✓**		36
7	**✓**			**✓**	36
8	**✓**				36

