## Discussion

In this study, we utilized the MOST framework to optimize a community-based intervention aimed at increasing help-seeking for depression care. Through a factorial design, our goal is to develop an effective intervention that raises awareness about depression, available services, and reduces stigma. The study will examine the impact and interaction of intervention components such as depression information, treatment awareness, dispelling myths, and life transformation experiences. The primary outcome will be changes in help-seeking behaviour, with treatment adherence as a secondary outcome.

The strengths of our study include the following: (i) the use of multiple methods and stakeholders in the development of the intervention, such as a systematic review, formative study, consultative workshops with various stakeholders, and pilot testing with a group of 10 FCHVs in another district; (ii) while most global mental health research focuses on developing and evaluating interventions to address supply-side barriers, this study targets demand-side barriers by using the innovative study design MOST, enabling us to evaluate the effectiveness of intervention components through an iterative optimization process; and (iii) the implementation of the intervention and study in multicultural, multilingual, and multi-ethnic communities in eastern Nepal, allowing for generalization of results throughout Nepal.

We anticipate challenges in maintaining intervention fidelity, as participants may seek additional information from FCHVs beyond what is included in the intervention packages or in a particular component. Additionally, ensuring fidelity in delivering the core components and the combination of intervention packages by the same FCHVs may be challenging. To address this, fidelity checklists will be used to guide delivery, and regular supervision sessions will be conducted to support FCHVs in maintaining fidelity.

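### The stated primary model has no term for the FCHV within whom allocation is done and does not test the component interactions the article says it will examine; the effect on main-effect tests is small

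*Protocol article*

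**What the plan says.** **Allocation.** Under Study design, participants "will be randomized into one of eight possible combinations of three candidate intervention components". Under Randomization, "The randomization will be conducted separately for each FCHV to ensure cases are allocated to all 8 factors", and "each FCHV will recruit between 8 and 10 participants". The same FCHV detects the participant and delivers whichever condition is drawn.

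**Primary analysis.** The outcome is a yes/no answer about seeking help. The Primary outcome paragraph of the analysis section specifies effect coding and says "General linear regression models will be used to test the main effects of the Gain Life intervention components". No paragraph of the analysis section names FCHV as a model term.

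**Interactions.** Study design justifies the factorial layout partly because it lets interactions between components be assessed. The Discussion says "The study will examine the impact and interaction of intervention components". The only interaction terms in the analysis section are those under Moderators, which concern socio-demographic factors.

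**Sample size.** "With 90% power and a significance level of 0.05, a total sample size of 288 participants is required, with 36 participants per condition", for 40% against 60% seeking help.

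**The concern.** An analysis should normally reflect the restrictions placed on the randomization. Here each FCHV is a block. Participants of one FCHV share a recruiter, a deliverer and a locality, so their outcomes are likely to be correlated. A model without FCHV leaves the between-FCHV variation in the residual, although the blocking has removed it from the component contrasts. The reported standard error then no longer matches the true one.

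The error can also go the other way. The Discussion expects difficulty in keeping the packages distinct when one FCHV delivers them all. If a component works better in some FCHVs' hands than in others', that variation belongs in the uncertainty of its average effect, and the stated model leaves it out. This matters because the article wants to generalize beyond the participating volunteers.

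The interaction gap is a different matter. The trial is meant to guide which components go forward. Whether one component adds anything once another is present bears on that choice, and the article says it will look at this but gives no analysis for it.

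**Working it through.** **Inputs from the article.** 40% versus 60%, alpha 0.05 (taken as two-sided), 90% power, 8 conditions of 36, so 144 versus 144 for each component. **Assumed, because the article gives no figure:** ICC from 0.01 to 0.20, and the between-FCHV spread of component effects.

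**1. The plan's own figure.** Per level, n = [1.96·√(2·0.5·0.5) + 1.2816·√(0.4·0.6 + 0.6·0.4)]² / 0.20² = (1.3859 + 0.8879)² / 0.04 = 129.3, so 130 and a total of 260. With continuity correction, n′ = (129.3/4)·[1 + √(1 + 4/(129.3·0.20))]² = 139.1, so 140 and a total of 280. That is within 3% of 288, so the stated size is reproduced for a main effect. Power at 144 versus 144 without correction is 92.8%.

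**2. Ignoring FCHV: common effects, complete blocks.** Reported SE = √(2·0.25/144) = 0.0589. True SE = 0.0589·√(1 − ICC). The ratio is 1/√(1 − ICC), and the true level is 2Φ(−1.96 × ratio). Power without FCHV is Φ[(0.20 − 1.96·0.0589) / (0.0589·√(1 − ICC))]. Power with FCHV is Φ[0.20/(0.0589·√(1 − ICC)) − 1.96].

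| Assumed ICC | SE too large by | True level | Power without FCHV | Power with FCHV |
|---|---|---|---|---|
| 0.01 | 0.5% | 4.9% | 92.5% | 92.7% |
| 0.05 | 2.6% | 4.4% | 92.9% | 93.6% |
| 0.10 | 5.4% | 3.9% | 93.5% | 94.7% |
| 0.20 | 11.8% | 2.8% | 94.6% | 96.7% |

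The largest loss is 96.7 − 94.6 = 2.1 points.

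**3. Incomplete blocks.** The article lists 24 + 30 = 54 FCHVs. At 8 to 10 participants each that is 432 to 540, not 288. A total of 288 fits 36 FCHVs × 8, or 288/54 ≈ 5.3 per FCHV. In simulation (4,000 trials per setting) with 54 FCHVs of 5 or 6 participants, power without and with FCHV fixed effects was 93.2% and 92.2% at ICC about 0.05, and 93.9% and 95.4% at ICC about 0.19. Fixed effects are therefore not always a gain.

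**4. Component effects that vary between FCHVs.** Zero average effect, 36 × 8, assumed SD of the effect-coded slope on the logit scale:

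| Slope SD | Type I error, stated model | With FCHV fixed effects, no clustering |
|---|---|---|
| 0.3 | 6.3% | 6.8% |
| 0.5 | 9.7% | 9.9% |
| 0.7 | 12.7% | 12.9% |

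An FCHV term alone does not cure this. Standard errors clustered by FCHV bring the level back to about 5–6% at a slope SD of 0.5.

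**5. Interactions and model family.** With complete blocks and no FCHV variation, simulated main-effect power was 93.2% for the linear model, 93.2% for logistic regression and 93.2% with all component interactions added. For a two-way interaction, a difference of differences of 0.20 has SE = √(4·0.25/72) = 0.118. Power is Φ(0.20/0.118 − 1.96) = Φ(−0.26), about 40%.

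**The case against.** A journal article condenses the full plan, and FCHV terms or secondary interaction tests could sit in an analysis plan that is not shown. The primary question asks which component works, so main effects are the right primary test, and nothing in the article excludes an interaction analysis. This stands in part. It means the FCHV point is a correction to the model as stated, not proof that FCHV will be ignored. It answers the interaction point less well, because the article announces that examination and its analysis section assigns interaction terms only to socio-demographic moderators.

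Three stronger readings are tempting, and the documents do not support them:

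- **That linear regression on a yes/no outcome gives wrong standard errors or loses power.** In balanced, effect-coded cells it matches logistic regression and estimates risk differences directly. The wording may also be loose for generalized linear. What remains is that model family and effect scale are not settled, and scale matters for interactions and moderators.
- **That leaving out interactions harms the main-effect tests.** With equal cells and effect coding, the terms are uncorrelated with the main effects.
- **That ignoring FCHV seriously damages power.** Losses of up to about 7 points appear only for effects of 14 to 16 points at an ICC of 0.20. The article plans for 20 points and gives no ICC.

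**Conclusion.** The point holds in a limited form. The stated primary model does not reflect the blocking by FCHV, and an announced interaction analysis has no stated method.

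For main effects the consequence is modest and, if component effects are common across FCHVs, on the safe side: at most about 2 points of power for ICC up to 0.20, with power above 90% throughout. The figures in the first table rest on complete blocks and an assumed ICC. Anti-conservative error arises only if component effects vary between FCHVs. That is plausible given the article's own remarks on fidelity, but the amount is unknown, and the 6–13% range follows from assumed spreads. The interaction gap leaves a stated aim unanswered and does not bias anything.

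None of this undermines the design or the sample size for main effects.

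**What to change.** In the Primary outcome paragraph of the analysis section:

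1. Include FCHV as a random intercept, preferred over fixed effects if blocks are incomplete, and cluster the standard errors by FCHV. The clustering is needed because the intercept alone does not protect against component effects that vary between FCHVs.
2. Add the effect-coded component-by-component interactions. Keep the main effects as the primary tests and label the interactions as low in power (about 40% for a 20-point two-way difference of differences).
3. State the model family and effect scale. A linear model for risk differences, or a logistic model reported as marginal risk differences, is acceptable.
4. Reconcile the number of FCHVs, the 8 to 10 participants each and the total of 288, so that the completeness of the blocks is clear.

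Do not carry the full interaction model over to adherence. That outcome rests on treatment initiators only: at 40% to 60%, about 115 to 173 of 288, or 14 to 22 per condition.

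Cost: wording only, since allocation lists are kept per FCHV and FCHV identity is therefore known. Clustering costs about 1 to 2 points of power, which can cancel the gain from the FCHV term at low ICC. The reason for the change is valid standard errors, not extra power.
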